## Abstract

**Background:**

The use of mental health mobile apps to treat anxiety and depression is widespread and growing. Several reviews have found that most of these apps do not have published evidence for their effectiveness, and existing research has primarily been undertaken by individuals and institutions that have an association with the app being tested. Another reason for the lack of research is that the execution of the traditional randomized controlled trial is time prohibitive in this profit-driven industry. Consequently, there have been calls for different methodologies to be considered. One such methodology is the single-case design, of which, to the best of our knowledge, no peer-reviewed published example with mental health apps for anxiety and/or depression could be located.

**Objective:**

The aim of this study is to examine the effectiveness of 5 apps (*Destressify, MoodMission, Smiling Mind, MindShift,* and *SuperBetter*) in reducing symptoms of anxiety and/or depression. These apps were selected because they are publicly available, free to download, and have published evidence of efficacy.

**Methods:**

A multiple baseline across-individuals design will be employed. A total of 50 participants will be recruited (10 for each app) who will provide baseline data for 20 days. The sequential introduction of an intervention phase will commence once baseline readings have indicated stability in the measures of participants’ mental health and will proceed for 10 weeks. Postintervention measurements will continue for a further 20 days. Participants will be required to provide daily subjective units of distress (SUDS) ratings via SMS text messages and will complete other measures at 5 different time points, including at 6-month follow-up. SUDS data will be examined via a time series analysis across the experimental phases. Individual analyses of outcome measures will be conducted to detect clinically significant changes in symptoms using the statistical approach proposed by Jacobson and Truax. Participants will rate their app on several domains at the end of the intervention.

**Results:**

Participant recruitment commenced in January 2020. The postintervention phase will be completed by June 2020. Data analysis will commence after this. A write-up for publication is expected to be completed after the follow-up phase is finalized in January 2021.

**Conclusions:**

If the apps prove to be effective as hypothesized, this will provide collateral evidence of their efficacy. It could also provide the benefits of (1) improved access to mental health services for people in rural areas, lower socioeconomic groups, and children and adolescents and (2) improved capacity to enhance face-to-face therapy through digital homework tasks that can be shared instantly with a therapist. It is also anticipated that this methodology could be used for other mental health apps to bolster the independent evidence base for this mode of treatment.

**International Registered Report Identifier (IRRID):**

PRR1-10.2196/17159

## Introduction

### Background

Mobile health apps for smartphones and tablet devices have become a lucrative business, with worldwide expenditure estimated to be over US $92 billion [1]. Apps are increasingly being used to monitor, assess, and improve mental health. There are now more than 10,000 publicly available mental health–specific apps [2]. Most of these apps lack published evidence for their effectiveness, making it difficult for clinicians and consumers to know which app is the most appropriate [3]. Currently, choices are made using reviews and ratings available in app stores [4], but these can produce unreliable results [5].

Although effective treatments for anxiety and depression exist, many people do not access these for various reasons [6]. However, with ownership of smartphones being at 70% of the global population and rising [7], mental health apps potentially offer a partial solution to limitations in service availability and acceptability.

### Previous Research

Published reviews have found that mental health apps can be effective for reducing anxiety [8] and depression [9] with an overall effect size of small to moderate [10]. Within this research, there are some notable shortcomings, including substantial heterogeneity across studies. For example, there have been differences in dosage [11,12] duration of interventions [13,14] and the absence of long-term follow-up data [15].

Another limitation of previous research is that most of it has been carried out by individuals who have developed the app, who have stood to gain financially from its sales, and/or who were otherwise associated with it [3]. For instance, a recent review of app stores found that only 1.02% of mental health apps offering therapeutic treatment for anxiety and/or depression had been evaluated using *independent* research [3]. Furthermore, in a meta-analysis of 9 studies on apps targeting anxiety [8] and in another meta-analysis of 18 studies on apps targeting depression [9], none involved independent research or replication (note that some studies were included in both meta-analyses).

A possible reason for the lack of research on apps is the time factor for large-scale experimental designs. Specifically, randomized controlled trials (RCTs) that demonstrate the efficacy of an intervention by measuring and comparing the outcomes of matched treatment and control groups are often lengthy to conduct. This is a barrier to achieving results in a time frame that is acceptable to the profit-driven app market. In the time it takes to complete an RCT, the app being studied may have been updated or disappeared from the market altogether as newer apps with enhanced features emerge in its place. Furthermore, RCTs are not necessarily the most appropriate study design for every situation, with another limitation of RCTs being lower ecological validity [16].

### Single-Case Designs

Single-case research designs address the issue of ecological validity by testing the effectiveness of an intervention for individuals (ie, performance under real-world conditions). However, single-case designs can also control for threats to internal validity and thus test for the efficacy of a treatment. Such designs go beyond a study with a sample of one participant and involve continuous and repeated measurements, random assignment, sequential introduction of the treatment, and specific data analysis and statistics [17]. Robust results in clinical psychology and behavioral science can be demonstrated when benefits are shown in 3 to 5 cases [18-20]. A single-case design is also safer than an RCT for vulnerable participants because their well-being is monitored by gathering and analyzing data more frequently during the study, and treatment can be altered if there is a clinically significant decline in status [21,22]. For mental health apps, single-case designs are a viable alternative for accelerating the evidence base [23,24].

### Objectives and Aims

The main objective of this study is to use a single-case design to examine the effectiveness of 5 mental health apps that purport to have efficacy for reducing symptoms of anxiety and/or depression.

This study seeks to answer the following research questions: (1) Do the apps in this study provide clinically significant improvements in symptoms of anxiety and/or depression? (2) What individual characteristics of participants influence the results in this regard? and (3) What individual characteristics of the apps influence the results?

The only hypothesis to be tested in this study is based on question 1:

Hypothesis 1: the use of apps will produce improvements in mental health and well-being in line with the 3-phase model of psychotherapy outcomes [25].

The Howard et al [25] model proposed that the outcome of any psychotherapeutic intervention will involve progressive reductions in subjective distress, then symptomatology, and, finally, an increase in overall life functioning.

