**Figure 1 figure1:**
[figure not shown]
Overview of the proposed study design.

This research will use a *prescribed dosage* approach, as if the app was a *digital antidepressant*: one 10-min *dose* of app use per day for 5 days per week. The 10-week intervention period creates equivalence with one 50-min session per week for 10 weeks, which is the annual maximum number of psychology sessions rebated under Australia’s Medicare system [27]. The rationale for a minimum 3-week postintervention period (to demonstrate the stability of the treatment effect) is similar to that described earlier, namely, that 20 daily SUDS ratings are needed for a valid data analysis. The justification for using the 5 chosen apps are as follows: (1) each has some evidence of efficacy published in a peer-reviewed journal, (2) all have publicly available free versions, and (3) all can fit the *prescribed dosage* approach. The chosen apps use 3 popular evidence-based frameworks employed across mental health settings for treating anxiety and/or depression: cognitive behavioral therapy (CBT), mindfulness, and positive psychology. Finally, the rationale for using 10 participants per app is that, even accounting for a 50% to 60% attrition rate [28], approximately 3 to 5 participants per app will provide enough data for a valid statistical analysis using time series conventions. As previously noted, this number of replications in a single-case design with similarly presenting individuals can produce robust and generalizable findings if the results are comparable in each case [18-20].

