All 50 participants (10 for each app) will be randomized to an app and their position in the single-case design (ie, P1 to P10) using the web-based random number generator, *Research Randomizer* [29]. The full inclusion and exclusion criteria are presented in Textboxes 1 and 2, respectively. A financial reimbursement will be offered to participants of Aus $0.50 (US $0.33) per daily SUDS rating sent via a text message. The researchers acknowledge that financial payments have the potential to interfere with ecological validity, because a person in the community would not normally be paid for using a mental health app, and intrinsic motivation, because people could potentially use the app for the benefit of financial remuneration rather than for the value of improving their mental health. However, the low amount of remuneration being offered of approximately Aus $45.00 (US $29.41) on average is not considered payment for participation in the proposed study but rather reimbursement of personal expenses incurred while taking part in the proposed study. Given that the effectiveness of mental health apps has the potential to benefit those from low socioeconomic groups, being reimbursed for providing in excess of 80 text messages will alleviate reasons that a potential participant of lower socioeconomic background could provide for being out of pocket for the cost of sending text messages from their mobile phone. Therefore, it is envisaged that prospective participants will more likely have motivation to improve their mental health beyond receiving financial remuneration. In addition, this financial incentive will not be advertised, and participants will only learn about this when they provide consent when completing the demographics questionnaire.

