#### Biographic and Demographic Features

The demographics questionnaire has been developed by the researchers to obtain information that will be examined to ascertain if any patterns in the outcome data are related to aspects of an individual’s demographic profile. Areas covered include mental health literacy [41], motivation to change [42], chronicity of anxiety and/or depression [43], and technology proficiency, all of which may influence results. Multimedia Appendix 3 contains the complete demographics questionnaire and all other measures used in this research.

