#### Visual Inspection

Visual inspection of plotted data allows for a personal judgment about the effect of an intervention and can often produce more meaningful information than approaches involving the calculation of statistical significance [20]. In this study, visual inspection will be possible using up to 112 data points of SUDS ratings, as illustrated in Figure 3. Data obtained from the uMARS will be plotted against participant ratings from the mental health and well-being outcome measures (DASS-21 and OQ-45.2) and SUDS data and inspected for any observed relationships.

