### Potential Added Value for Clinicians and Consumers

This study is unique with respect to any published study of mental health apps that could be located. This independent research, using a single-case methodology, allows for an in-depth examination of personal factors that may impact the effectiveness of these apps. It will therefore add value to existing studies on these specific apps. However, it is also anticipated that this research will be automated to the point where the design can be used to examine larger samples with the rigor of an RCT experimental design, thereby having a positive impact on increasing future research at a faster rate. It also provides an opportunity for evidence-based mental health treatment to reach those who are not already receiving it.

If mental health apps have demonstrated effectiveness, they could be incorporated by clinicians into face-to-face therapy to enhance the experience of consumers. For example, some apps allow users to complete homework tasks set by their therapist or to make thought diary entries that can be shared digitally with their therapist. Other information such as physiological readings and user-entered information such as SUDS ratings can also be sent digitally to clinicians to gain a more accurate reading of their client’s emotional health between sessions [68].

There are potential benefits for health systems and mental health consumers if apps can gain increased legitimacy for their ability to effectively manage anxiety and depression. These include the following: more economical for low socioeconomic groups to obtain mental health treatment compared with face-to-face services [69], improved access for those in rural areas where there may be limited treatment options [70], reduced stigma [71] because of anonymous assistance, access for children and adolescents who are already large consumers of smartphones and the internet [72], and it is simply a preferred way to receive mental health information for some [73]. Therefore, it is important to increase research on the efficacy and effectiveness of mental health apps using appropriate and scientifically validated methodologies in addition to RCTs, as the widely considered gold standard of RCTs may not be the most appropriate for analyzing mental health apps [23,74].

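### Questions 2 and 3 ask what *influences* results, but an open descriptive search in about 20 to 25 completers and five apps can show associations only

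*Protocol article*

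**What the plan says.** Objectives and Aims names three questions. The second is "What individual characteristics of participants influence the results in this regard" and the third is "What individual characteristics of the apps influence the results". The text then limits confirmatory work: "The only hypothesis to be tested in this study is based on question 1".

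The methods for questions 2 and 3 are in three places:

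- **Biographic and Demographic Features:** questionnaire data "will be examined to ascertain if any patterns in the outcome data are related" to a person's profile. Four areas are named (mental health literacy, motivation to change, chronicity, technology proficiency) in a list that is not closed.
- **Descriptive Statistics and Qualitative Accounts:** descriptive statistics support the other techniques, and the uMARS helps to understand participants' attitudes to their app.
- **Visual Inspection:** uMARS data are plotted against DASS-21, OQ-45.2 and SUDS and "inspected for any observed relationships". The same section says that visual judgment can often be more informative than significance calculations.

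On numbers, Study Design expects that "approximately 3 to 5 participants per app will provide enough data for a valid statistical analysis" after 50% to 60% attrition. Potential Added Value for Clinicians and Consumers says that the method "allows for an in-depth examination of personal factors that may impact the effectiveness of these apps". Limitations and Strengths has a general caveat on generalizability but nothing specific to questions 2 and 3.

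**The concern.** *Influence* is a causal word. To answer it, a design needs characteristics that vary independently of other explanations, are measured before the outcome, and are examined in a way that separates signal from chance. The two questions fall short in different respects:

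- **Chance.** Many pairings are looked at in few people, and what is reported is whatever appears. The largest of many null correlations in a small sample looks like a moderate relationship.
- **Confounding (question 3).** The five apps differ at once in framework, developer, country, aesthetics and activities. A difference between apps cannot be assigned to any one of these.
- **Timing (question 3).** The uMARS is completed at the end of the intervention phase, at the same point as the DASS-21 and OQ-45.2. A person who feels better may rate the app more highly for that reason.

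At stake is the conclusion drawn on two of the three study questions. A chance or confounded pattern could be written up as a reason why an app works or for whom it works.

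**Working it through.** **Completers.** Inputs from Study Design: 10 participants per app, 50% to 60% attrition, five apps.

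- Per app: 10 × (1 − 0.50) = 5 and 10 × (1 − 0.60) = 4.
- Total: 5 × 5 = 25 and 5 × 4 = 20.

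The article's figure of about 3 to 5 per app is reproduced to within rounding. Its lower end, 3 per app or 15 in total, would need 70% attrition, so 20 to 25 is used here.

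**Pairings.** Four named participant areas plus five uMARS subscales make 9 characteristics. With three outcome measures (SUDS, DASS-21, OQ-45.2) there are 9 × 3 = 27 pairings. Counting DASS-21 depression and anxiety separately gives 9 × 4 = 36. Because the list of areas is open, these are minimum counts.

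**What an inspector sees when nothing is there.** In simulated data with no true relationship (4,000 data sets per setting, normal variables, 9 characteristics, 3 outcomes), the median of the largest absolute correlation was:

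| Completers | Independent variables | Correlation 0.5 within each set |
|---|---|---|
| 20 | 0.50 | 0.46 |
| 25 | 0.45 | 0.41 |

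This uses no significance threshold. It describes the strongest pattern that would be visible.

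**Precision of a single pairing.** By Fisher's z, the 95% limits around an observed correlation of zero are ± tanh(1.96/√(n − 3)). For n = 20 this is ± tanh(0.475) = ± 0.44, and for n = 25 it is ± tanh(0.418) = ± 0.40. A true correlation of 0.59 (n = 20) or 0.54 (n = 25) would be needed for 80% power in a two-sided 5% test.

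**Illustration only: if tests at P<.05 were run.** With 27 independent pairings, the chance of at least one false positive is 1 − 0.95^27 = 0.75, with 27 × 0.05 = 1.35 expected. With correlation 0.5 within each set, the simulated chance is 0.56 to 0.57. The article plans no such tests.

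**App features.** The Discussion gives two CBT apps, two mindfulness apps and one positive psychology app.

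- Positive psychology is represented by *SuperBetter* alone, that is, by about 4 to 5 completers who all used the same product. Its framework cannot be told apart from its game-like style or its developer.
- The other two frameworks have two apps each, and the article describes these as differing in origin, aim and activities.
- For a feature fixed within an app, the unit is the app. With n = 5, a correlation must exceed 0.88 to reach P<.05.

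**uMARS timing.** Under Procedure, the uMARS is completed at the end of Phase 3 with the DASS-21 and OQ-45.2. The postintervention and 6-month measures come later, but the rating still follows ten weeks of experienced change, which those later scores partly carry forward.

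**The case against.** The strongest case on the other side is that the article already puts questions 2 and 3 outside hypothesis testing, in the sentence that follows them. No correlation, P value or threshold is planned for either. The only .05 criterion that it spells out concerns the individual reliable change index. Its language is otherwise tentative: characteristics *may* influence results, and personal factors *may* affect effectiveness. The figure of 3 to 5 completers per app is offered for time series replication, not for an analysis of moderators. No contrast between frameworks is announced, and uMARS ratings vary by participant, so five is not the only sample size. Participants are also randomized to apps: "All 50 participants (10 for each app) will be randomized to an app and their position in the single-case design". Finally, a fuller plan that is not shown may list the analyses.

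Most of this stands, and it rules out two readings that a reader might infer. One is that the plan contains a family of significance tests with a false-positive rate far above 5%. The documents do not support that, and the rates above are illustrations. The other is that the article claims to identify determinants of effectiveness. It poses questions and hedges them.

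The core is not removed. Leaving a question without a hypothesis is not the same as calling it exploratory, and the article gives visual patterns evidential weight. Randomization supports comparing the apps as whole packages; it does not separate the features within a package. It also does not assign participant characteristics. A more detailed analysis plan could close the list of pairings, but it could not remove the confounding of features with apps or change when the uMARS is completed.

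**Conclusion.** The point holds in a limited form. Questions 2 and 3 are worded causally, while the design and stated methods can deliver descriptive associations only. With 20 to 25 completers and at least 27 pairings, the strongest visible pattern under no true relationship would typically be a correlation of about 0.41 to 0.50. That range assumes normal variables and a correlation of 0 to 0.5 within each set. For question 3, framework and other fixed features are inseparable from the five apps, whatever the analysis. End-of-treatment uMARS ratings leave the direction of any association open. The limitations cover none of this.

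The analysis of question 1 is not affected. The severity is optional to moderate: it concerns wording, reporting and what may be concluded.

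**What to change.** 1. **Objectives and Aims:** state questions 2 and 3 as hypothesis-generating, asking which characteristics *are associated with* results.
2. **Biographic and Demographic Features, and Visual Inspection:** report every pairing of the named characteristics and the five uMARS subscales with the study's outcomes, each with an interval, whether or not a pattern is seen. Keep SUDS, DASS-21 and OQ-45.2 all in. Restricting the search to DASS-21 would shorten the list but would conflict with the three-phase outcome model on which the study rests.
3. **uMARS:** describe any relationship with outcome as an association with a rating made at the end of treatment.
4. **App differences:** report results by app, and do not attribute differences to framework or design features.
5. **Limitations and Strengths:** add a sentence on chance findings in a small sample, confounding of features with apps, and the timing of the uMARS.

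The cost is slightly more analysis and tabulation and a weaker stated claim for two of the three questions. No new data are needed.

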#### Mental Health and Well-Being

A 3-phase model of psychotherapy outcomes [25] is applied.

Subjective well-being: SUDS ratings—participants rating their well-being in response to the question, “How do you feel today?,” with 0 indicating no distress and 10 indicating worst distress [44].Symptoms: the Depression Anxiety Stress Scale-21 short-form version (DASS-21) [45]. Participants rate their experience of symptoms of depression, anxiety, and stress over the previous week on a 4-point scale, ranging from 0 (did not apply to me at all) to 3 (applied to me very much or most of the time). Items in each subscale are summed to provide scores for symptoms of depression and anxiety, with higher scores indicating greater severity of symptomatology. The total scores for depression and anxiety subscales are multiplied by 2 to interpret the norms [46,47]. Severity ratings for the depression subscale are 0-9 (normal), 10-13 (mild), 14-20 (moderate), 21-27 (severe), and ≥28 (extremely severe). Norms for the anxiety subscale were set as 0-7 (normal), 8-9 (mild), 10-14 (moderate), 15-19 (severe), and 20+ (extremely severe). The DASS-21 has been shown to demonstrate sound psychometric properties and validity [48].Life functioning: the Outcome Questionnaire-45 second edition version (OQ-45.2) [49] is a 45-item self-report scale that measures overall interpersonal relationships and social role functioning in adults aged 18 years and older [50]. An index for overall life functioning is calculated [51]. Participants rate their feelings over the previous week on a 5-point scale, ranging from 0 (never) to 4 (always). The scale consists of both positive and negative items that are reverse-scored; higher scores indicate greater symptoms of distress and difficulties in interpersonal relations. A total score of ≥63 is indicative of clinically significant symptoms, with the subscale cutoffs for clinical significance being 35 for symptom distress, 14 for interpersonal relations, and 11 for social role [51]. The OQ-45.2 has demonstrated high internal consistency (α=.90) and test-retest reliability of *r*=.84 over a minimum 3-week period [52]. The OQ-45.2 has also shown good construct and concurrent validity in a community sample when using the total score as opposed to interpreting the 3 individual subscales [53].

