#### Phase 1 (Prebaseline)

Web-based links to the information sheet for participants and consent form, the demographics questionnaire, and the mental health and well-being outcome measures (DASS-21 and OQ-45.2) are sent by email and SMS text messages and completed digitally by participants using the Qualtrics survey platform [55] and the OQ-Analyst platform [56]. Participants are screened for suitability to be in the proposed study by having their outcome measure and demographics questionnaire responses analyzed for evidence of severe anxiety and/or depression, suicidal ideation, or the presence of other severe mental illnesses such as psychosis. If researchers require further information from any participant, the participant will be contacted to clarify any queries or concerns. If a participant is deemed inappropriate for the proposed study, she/he will be directed by the researchers toward more appropriate forms of care.

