#### Phase 2 (Baseline)

Accepted participants provide daily SUDS ratings for a minimum of 20 days or until a stable baseline profile of current psychological distress is achieved. At the end of this phase, the mental health and well-being outcome measures (DASS-21 and OQ-45.2) are completed.

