#### Phase 3 (Intervention)

Participants are provided with generic instructions for all apps, links to both the Apple App Store and Google Play Store for their app, and specific instructions on how to use their app once it is downloaded (Multimedia Appendix 2). In addition, website links to information on the type of evidence-based framework their app uses and emergency contact information in the event of a mental health crisis are provided. Participants continue to supply daily SUDS ratings for the minimum 10-week intervention. Data analysis will be ongoing throughout this phase and will be used to assist in determining whether any participant’s mental health is significantly deteriorating. If a participant provides a SUDS rating of 10 for 2 consecutive days, they will be contacted for a check on their welfare. Similarly, if a participant’s SUDS ratings are above 8 for 5 consecutive days, they will also be contacted for a check on their welfare. We have chosen these cutoff values because the information provided to participants about the SUDS indicates that 8 is equal to their perception of feeling *very distressed* and 10 is equal to their perception of feeling the *worst distress.* The SUDS does not have a universal categorization label for each point on the scale, in addition to the number. Instead, it was designed to allow flexibility in an individual’s self-assessment [57] and labeling can vary from study to study. The mental health and well-being outcome measures (DASS-21 and OQ-45.2) and uMARS are completed at the end of this phase. If a participant’s responses on the outcome measures reveal a clinically significant decline in mental health compared with their responses at the beginning of the intervention, which places them in a severe category of mental illness, she/he will be contacted for a check on their welfare. In all cases, if a participant is categorized as being inappropriate for continuation in the proposed study, she/he will be directed toward more appropriate forms of care.

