#### Phase 4 (Postintervention)

Participants provide SUDS ratings for at least 20 days following the completion of their official intervention period. Once a minimum of 20 SUDS ratings have been received, they will complete another DASS-21 and OQ-45.2. Participants are given information on all the apps so that they may explore the others if they wish.

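### Hypothesis 1 invokes an ordered model of change, but the assessment schedule cannot resolve that order during the 10 weeks of app use and shows it only coarsely afterwards

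*Protocol article*

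**What the plan says.** Objectives and Aims announces a single hypothesis ("The only hypothesis to be tested in this study is based on question 1"): "the use of apps will produce improvements in mental health and well-being in line with the 3-phase model of psychotherapy outcomes". The next sentence describes that model as "progressive reductions in subjective distress, then symptomatology, and, finally, an increase in overall life functioning".

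Mental Health and Well-Being applies the model by giving each step one instrument: SUDS for subjective well-being, DASS-21 for symptoms and OQ-45.2 for life functioning.

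The Procedure fixes when each is measured. SUDS is daily through baseline, intervention and postintervention. The two questionnaires are always paired:

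- Phase 1: "the demographics questionnaire, and the mental health and well-being outcome measures (DASS-21 and OQ-45.2) are sent by email and SMS text messages".
- Phase 2: "At the end of this phase, the mental health and well-being outcome measures (DASS-21 and OQ-45.2) are completed".
- Phase 3: "The mental health and well-being outcome measures (DASS-21 and OQ-45.2) and uMARS are completed at the end of this phase".
- Phase 4: "Once a minimum of 20 SUDS ratings have been received, they will complete another DASS-21 and OQ-45.2".
- Phase 5: both again at 6 months.

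The analyses described are a time series of SUDS and a Jacobson-Truax classification of DASS-21 and OQ-45.2 across phases.

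**The concern.** A claim about the order of change needs measurements taken between the changes. In the period when the app is prescribed, only one of the three domains is measured. Symptoms and functioning are recorded at its two ends, always on the same occasion.

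The risk is a result that looks more like the model than the data warrant. A plot of daily SUDS can show movement in the first weeks. The questionnaires cannot register any movement before the end of the intervention. A reader who sees SUDS fall early and both questionnaires improved at week 10 could take this as support for distress changing first, although the same picture would arise if all three domains had moved together.

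The schedule is fixed in this document, and no later analysis plan can recover order from measurements that were not taken. Limitations and Strengths does not mention the point. It counts covering the three domains at several time points as a strength.

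**Working it through.** **1. Reproduce the schedule.** The Procedure gives prebaseline, end of baseline, end of intervention, postintervention and 6 months: 5 joint occasions, matching the five stated under Expected Time Frames. The duration also agrees: 3 + 10 + 3 + 24 = 40 weeks, or 42 with 26 weeks for 6 months, against a stated total of about 40.

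**2. Place the occasions on a time axis from app start.** End of baseline = 0; end of intervention = 10; postintervention = 10 + 20/7 = 12.9; 6 months = 12.9 + 26 = 38.9 weeks (counting the 6 months from postintervention is an assumption). Occasions strictly between 0 and 10: none. Both questionnaires ask about the previous week, so the week-10 answers cannot date an earlier change.

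**3. Rule for visibility.** Let S be the week in which symptoms change and F the week in which functioning changes. The order S before F can be seen only if some assessment g satisfies S ≤ g < F. If both fall between 0 and 10, no such g exists. The same holds for distress against symptoms: SUDS can be dated, but a DASS-21 change within weeks 0-10 is known only to lie somewhere in that interval.

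**4. Fixed examples.**

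| Symptoms change | Lag to functioning | Order visible? |
|---|---|---|
| week 3 | 2, 4 or 6 weeks | no |
| week 3 | 8 weeks | yes |
| week 6 | 2 or 4 weeks | no |
| week 6 | 6 weeks | yes |
| week 8 | 2 weeks | no |
| week 8 | 4 weeks | yes |

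**5. How often, under assumed times.** The documents give no change times, so S was taken as exponential with mean 4, 6 or 8 weeks, and the lag as an independent exponential, with no measurement error. Simulation (100,000 draws per setting) gave:

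| Mean lag | Order visible | Expected among 3 to 5 analysable participants per app |
|---|---|---|
| 2 weeks | 10-14% | 0.3 to 0.7 |
| 4 weeks | 24-27% | 0.7 to 1.4 |
| 8 weeks | 45-46% | 1.4 to 2.3 |
| 12 weeks | 57-58% | 1.7 to 2.9 |

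The last column multiplies the lower percentage by 3 and the upper by 5, the range of analysable participants that Study Design expects.

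Hand check of one setting (mean S = 4, mean lag = 2). With rates a = 1/4 and b = 1/2, the chance of spanning week g is a/(a − b) × (e^(−bg) − e^(−ag)).

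- At g = 10 this is e^(−2.5) − e^(−5) = 0.082 − 0.007 = 0.075.
- Spanning postintervention with S after week 10 adds e^(−2.5) × (e^(−0.714) − e^(−1.429)) = 0.082 × 0.250 = 0.021.
- The 6-month occasion adds almost nothing.

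The sum is 0.096, or 10%, as simulated.

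**The case against.** The strongest reply is that three joint occasions follow app start and the instruments are scored separately, so the data can speak to order. DASS-21 improved at week 10 with OQ-45.2 following only at postintervention or 6 months would support the model. OQ-45.2 improved at week 10 with DASS-21 unchanged, or DASS-21 improved while SUDS stays flat, would count against it. This stands. A reader might infer that the order cannot be tested at all, or that Hypothesis 1 cannot be refuted; the later occasions show that neither is so. They have limits, however. They fall after the prescribed app period, and in Phase 4 participants receive information on all the apps and may try others, so a late gain in functioning is harder to credit to the assigned app.

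A second reply is that order may not be claimed. The hypothesis is said to rest on question 1, which asks only about clinically significant symptom improvement, and Principal Findings restates the expectation without order. That is fair, and it is why rewording is enough. But the hypothesis as written refers to the model, and the model is described by its sequence.

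Three further inferences are not supported:

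- That the plan will report a false lag of a given number of weeks. This would need an analysis that dates questionnaire change to the assessment day and compares it with SUDS onset, and none is stated.
- That the absence of a stated timing comparison is itself a fault. An analysis plan that is not shown may supply it.
- That the subscale cutoffs ("with the subscale cutoffs for clinical significance being 35 for symptom distress, 14 for interpersonal relations, and 11 for social role") show how far the OQ-45.2 total is driven by symptoms. Cutoffs are not weights, and they sum to 35 + 14 + 11 = 60, not to the total cutoff of 63. The total does contain a symptom-distress subscale, so some overlap with DASS-21 is real, but its size cannot be derived from these figures.

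**Conclusion.** The point holds in a limited form. During the 10-week intervention the schedule cannot resolve order between symptoms and functioning, or show whether distress moved before symptoms when both change in that window. After it, order is visible only when a lag spans one of three assessments.

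That no joint occasion falls within the intervention follows directly from the Procedure and needs no assumption. The percentages depend on assumed exponential times and lags, a 6-month point counted from postintervention, and error-free detection of change. They range from about 10% to 58% and indicate scale only. For lags of a few weeks, an app with 3 to 5 analysable participants would often have one informative participant or none.

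The SUDS time series and the Jacobson-Truax classification, as tests of improvement, do not depend on order and are unaffected. What is affected is any conclusion that the results followed the sequence of the model.

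**What to change.** Preferred: restate Hypothesis 1 as improvement in each of the three domains (SUDS, DASS-21, OQ-45.2) with no claim about order. This agrees with question 1 and with Principal Findings, and costs only wording.

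If the order claim is kept, add joint DASS-21 and OQ-45.2 occasions within the intervention, for example at the ends of weeks 3 and 6. Compare the first occasion of reliable change across domains, with SUDS averaged over the same weeks so that all three are judged on the same grid. The cost is 2 instruments × under 10 minutes × 2 occasions, at most about 40 extra minutes per participant. Order would still be seen only to within a few weeks.

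In either case keep the OQ-45.2 total as the functioning measure, because the validity evidence cited under Mental Health and Well-Being favours the total over the subscales. State its overlap with symptom distress, and report the interpersonal-relations and social-role subscales as supportive only. If the schedule is left as it is, add to Limitations and Strengths that an earlier change in SUDS may reflect its daily sampling.
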